### Randomization

All participants who meet criteria and who give informed consent are randomized to the experimental condition (exposure to fashion magazines) or control condition (exposure to neutral magazines) based on the randomized block/split-plot design approach (Lane 2008). Randomization is performed at the study center at the Department of Psychology in Fribourg. The randomization is stratified by age. The allocation ratio between the two conditions is 1:1.

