### Study design

This study is a multi-site cross- and longitudinal experimental trial examining the impact of exposure to the thin ideal (body image, affect, eating behavior, psychophysiological stress-response) using a standardized laboratory waiting room design (Turner et al. 1997). The design favors daily real life situations (high ecological validity) and foregoes a computerized presentation of thin ideals. Participants suffering from AN and BN vs. patients with mixed mental disorders vs. healthy control groups (between subject factor) are tested during a media exposure and during a non-media exposure condition (between and within subject factor) over time (Pre-Post; within subject factor) in order to examine stability of expected effects three months later. This time span corresponds to an approximated mean treatment duration for AN and BN patients in collaborating Swiss and German clinics. Treatment components are assessed based on the German evidence based guidelines for diagnosis and treatment (Herpertz et al. 2011). Treatment components are double checked by therapists and patient-ratings (Bandelow et al. 2013; DGPPN et al. 2009; Schaefert et al. 2012; Becker et al. 2013).

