### Participants

Altogether 250 participants will be included in the study. Healthy participants (N = 100) as well as participants suffering from AN (N = 50), BN (N = 50) or mixed mental disorders (depressive, SSD and anxiety disorders; N = 50) will be randomly distributed to either a thin ideal or neutral exposition based on magazine viewing (Figure 2). All participants will be evaluated regarding the presence of any mental disorder during face to face interview based on the Structured Clinical Interview for mental disorders currently adapted for DSM-5 by the [name] group, DIPS for DSM-5 (see Table 1 for an overview of all interviews and psychological questionnaires).

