**Figure 3 Fig3:**

**Times schedule.**

### Experimental procedure

1. Preparation phase: During the preparation phase of 35 minutes, participants are asked to dispense the first saliva sample, to run the emotion recognition task (*decode*_*EMO*), to put on the ECG belt to assess HR, to fill in the sociodemographic questionnaire ([name] et al. 2007) and self-report measures of body image, affect and eating behavior (*pre media exposure*).

Assessment of biological measures: Measurement of salivary cortisol and alpha-amylase concentrations during and after media exposure will be performed 9 times. The sampling protocol was chosen to capture peak and recovery of salivary alpha-amylase, as well as salivary cortisol (Kirschbaum & Hellhammer 1989; Nater & Rohleder 2009). The participants will be instructed to place the cotton roll in a specific area of the mouth for 2 minutes and chew on it and to avoid physical exercise, eating or drinking anything but water, brushing teeth or smoking for at least 1 hour before examination. Medication, somatic and mental diseases, date of last menstruation, last alcohol consumption and habitual smoking will be documented. HR will be measured continuously using ambulatory monitoring systems such as Movisens (www.movisens.com). Belts will be put on at the beginning of the experimental procedure and will be worn during the whole procedure. To minimize artifacts (e.g. orthostatic reaction) we analyze HR as well as HRV after a rest of two minutes after changing the position (e.g. going from room 2 into room 3). Start and end points of different stages of the experiment will be marked using corresponding software.

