### Covariates

Depending on the specific hypothesis, analyses will be adjusted for covariates: baseline values of depression (BDI-II) and anxiety (BAI); eating disorder pathology (EDE-Q, DEBQ); socio-economic status, (SES); BMI, internalization of thin ideal (SATAQ-G); trait and correlates of acute appearance schema activation (ASI-R); SSD symptoms (SOMS) self-esteem (RSES), presence of comorbid mental disorders (DIPS). We will further take into account the role of Social Comparison Processes (PACS) and Third-Person Perception (TPP), which has been shown to influence the effects of media exposure in healthy young individuals in media psychology research.

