### Methodological aspects

#### Power analysis

Sample size calculations are based on findings of small to medium effects of mass media engagement on body image in young adults from the general population (Levine & Murnen 2009) and based on findings from our pilot study, using the software G*Power, version 3.13 (Faul et al. 2007), and assuming two-sided tests with Alpha = .05 and Beta = 0.2 (Power = 0.8). Hypotheses H-1.1 and H-1.2 assuming changes in the subjective and physiological state due to the exposure to the thin ideal correspond to the main effect experimental condition on pre-post exp.-differences. In the pilot study these changes were moderate to large for the subjective states (affect, body image). Assuming such an effect size in the population (*Cohen*’*s f* > 0.30, which can be computed from ɳ^*2*^) the required sample size would be 90, (45 in each condition) to ensure a power > .80. Changes in the physiological variables were small in the pilot study (*f* < .16) and would require a larger sample size of at least 309 participants. However, the experimental manipulation is further qualified. H-1.2 predicts that effects of the thin ideal induction are stronger for patients than for non-patients. This is indicated by an interaction effect (group * condition; contrast: healthy vs. patients), which was small in the pilot study (*f* < .18). Thus the total sample size should be at least 245. H-1.3 predicts differences between the clinical groups and indicated by an interaction effect too (group * condition; contrast: BN + AN vs. clinical control). Due to the rather small number of patients in the pilot study, different diagnostic groups were not compared to each other. Differences between patients with eating disorders and the clinical comparison group are assumed to be small to moderate and thus sample requirements will be similar. With a sample of size of N = 250 also small to medium moderator effects (H-1.4) (Figure 1) could be detected.

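### Age, the stated randomisation stratum, and site are not in the pre-specified covariates or model factors; the tests stay valid, and the possible loss of precision is small (minor)

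*Protocol article*

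**What the plan says.** All references are to the protocol article.

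- **Randomization.** "The randomization is stratified by age". Allocation is 1:1 under a block or split-plot approach. The age bands and the blocking factor are not given.
- **Study design.** "This study is a multi-site cross- and longitudinal experimental trial". Under Recruitment, patients come from Swiss and German clinical units, and healthy controls come from Fribourg.
- **Covariates.** Depending on the hypothesis, "analyses will be adjusted for covariates: baseline values of depression (BDI-II) and anxiety (BAI"), followed by EDE-Q, DEBQ, SES, BMI, SATAQ-G, ASI-R, SOMS, RSES and comorbidity, with PACS and TPP also considered. That is 13 variables, and neither age nor site is among them.
- **Data analytic plan.** The factors are exposure, group (four levels) and two pre-post factors. Further covariates may be included at discretion, and none is named. In the H-1.4 moderator model, group itself is optional.

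**The concern.** Stratifying on a prognostic variable removes its contribution to the chance difference between conditions. A model without that variable still counts its variance as residual error, so the standard error is larger than the design warrants. The test keeps its type I error below the nominal level and gives up some power. The same argument for adjusting applies to site, in so far as outcomes differ between sites.

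Power is the point at stake because there is little slack. The H-1.2 interaction is said to need 245 participants and 250 are planned. The article also commits itself to a long, specific adjustment list, and the one variable known to have shaped the allocation is not on it. A choice left to discretion is also weaker than one fixed before the data are seen.

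**Working it through.** **Inputs from the Power analysis and Participants sections.** The tests are set up "assuming two-sided tests with Alpha = .05 and Beta = 0.2 (Power = 0.8"). The H-1.2 interaction effect is one "which was small in the pilot study (*f* < .18"), and the conclusion drawn is "Thus the total sample size should be at least 245". Group sizes are healthy 100, AN 50, BN 50 and mixed disorders 50. I take f = .18, the upper bound given.

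**Input assumed.** R² is the share of residual outcome variance, after group and pre value, that age or site explains. The article gives no figure, so I show 0 to 0.10.

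**1. Reproduce the plan's own figures.** I used a noncentral F test with 1 numerator degree of freedom and λ = f²N. The required totals are 90 for f = .30, 309 for f = .16 and 245 for f = .18, all matching the article. For f = .18, λ = 0.0324 × 245 = 7.94 and power is 80.1%. At N = 250, λ = 8.10 and power is 80.9%. The sample size arithmetic is sound.

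**2. Effect of adjustment.** Adjusting replaces f by f/√(1 − R²), so λ = 8.10/(1 − R²) at N = 250. For an exposure test that ignores a fully balanced stratum, true alpha = 2 × [1 − Φ(1.96/√(1 − R²))].

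| Assumed R² | λ at N = 250 | Power with adjustment | N needed for 80% | True alpha if unadjusted |
|---|---|---|---|---|
| 0 | 8.10 | 80.9% | 245 | .050 |
| 0.02 | 8.27 | 81.7% | 240 | .048 |
| 0.05 | 8.53 | 82.9% | 233 | .044 |
| 0.10 | 9.00 | 84.8% | 221 | .039 |

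The alpha column is for the exposure main effect and assumes complete age balance. Coarse age bands would balance only part of the age effect and leave alpha nearer .050. For the group-by-condition contrasts it applies only as far as age is balanced within groups.

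**3. Price of extra terms.** At N = 245 and f = .18, power is 80.13% with 2 cells in the model and 80.12% with 8. Six degrees of freedom therefore cost about 0.01 points.

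**4. If allocation had ignored diagnostic group.** With exact 1:1 within groups, the H-1.2 contrast (weights 1, −1/3, −1/3, −1/3) has variance proportional to 2/50 + 3 × (1/9) × (2/25) = 0.0667. H-1.3 (weights ½, ½, −1) has 2 × ¼ × (2/25) + 2/25 = 0.12. I compared these with 100,000 simulated allocations blind to group, either simple or balanced 125:125 overall.

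- **H-1.2:** variance rises on average by 1.1–1.5%, and power goes from 80.9% to 80.4–80.5%.
- **H-1.3** (f = .18 assumed here too): variance rises by 1.7–2.1%, and power goes to 80.1–80.3%.
- **At the 95th percentile of imbalance:** power is 79.5–79.8% (H-1.2) and 78.5–78.9% (H-1.3).

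**The case against.** The strongest reply is that a condensed article need not list every model term. The covariates depend on the hypothesis, and the Data analytic plan leaves room for more. That disposes of one tempting inference, that the trial refuses to adjust for the items under Experimental procedure ("Medication, somatic and mental diseases, date of last menstruation, last alcohol consumption and habitual smoking will be documented"). Silence there is not exclusion, and the saliva and heart-rate outcomes are secondary. It is less persuasive for age, because the article does give both a stratum and a specific list and the two do not match.

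A second reply is that age may hardly matter. The range is 18 to 35, patients are age matched, and the outcome may be analysed with its pre value as covariate. This stands: R² could be close to zero, and then nothing is lost.

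A reader might also infer that age is the only stratum and that balance within the 50-person groups is left to chance. The text does not support this. The block design has no named blocking factor, and the Participants section lists the four groups with their sizes before saying they are randomised, which is compatible with allocation within group. The chance of a 20:30 split or worse in a group of 50 is 20% under simple randomisation and 15% if only the overall total is balanced. Neither figure applies if blocks sit within group.

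**Conclusion.** The point holds, and it is minor. As written, the plan stratifies on age in a multi-site trial and pre-specifies neither age nor site in the analysis. The consequence is conservatism and lost precision, not bias: true alpha between .050 and about .039, and at most about 3.9 points of power forgone (84.8 − 80.9), for an assumed R² of 0 to 0.10. The article gives no R², and the loss may be nil.

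The documents do not support a stronger conclusion that diagnostic group was neglected in a way that harms the key contrasts. Group is a factor in the main model, so no bias follows there. Even if allocation ignored it, the expected cost is about 1–2% of information for H-1.2 and H-1.3, or 0.4–0.8 points of power. Nor is group the interacting factor throughout: in H-1.4 the interaction is with the moderator. The sample size figures themselves are correct.

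**What to change.** Add to the Data analytic plan that the exposure models for all hypotheses include age, coded as in the stratification, and site as fixed effects, whatever other covariates are used. State the age bands and the blocking factor in the Randomization section, so that the reader can see whether allocation was within group.

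The cost is wording and a few degrees of freedom. One caution belongs in the text: all healthy controls come from Fribourg, so a site term is partly confounded with the healthy-versus-patient group main effect, and that main effect should be read accordingly. Exposure is randomised, so the exposure comparison does not share this problem. No change to the allocation scheme of this ongoing trial is required.

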### Blinding

Interviews are performed by two doctoral students in Switzerland and Germany under the supervision of the respective post doc and the principal and co-investigator. Interrater reliability is routinely assessed and guaranteed (kappa no lower than .60). Blinding of different, independent interviewers is not feasible, as this would impede clinical routine of the collaborating clinics. Interviewers and experimenters have no academic or therapeutic relationships with the participants. Computerized versions of self-reports and psychological questionnaires are filled in by patients individually during the experiments.

### Data analytic plan

The design of the study refers to a mixed four-way factorial ANOVA with exposure type (“exposure”, two levels) and study group (“group”, four levels) as between-subjects, and pre-post-exposure phase (“prepost-exposure”, two levels) and pre-post-intervention phase (“prepost-treatment”, two levels) as within-subjects factors. This model may be simplified to a three-way ANOVA by analyzing the two time points pre- and post-treatment separately. It can further be simplified to a two factorial model if, the pre-post-exposure difference is analyzed, using the pre values as a covariate (Vickers & Altman 2001). Additional further covariates can be added to the model if necessary. In the case of hypothesis 1.4, the principle model contains the factors exposure and prepost-exposure plus the moderator of concern, while the factor group can be added if required. Note that we will use linear mixed models to analyze the data as these types of models have been shown to have more statistical power to detect actually existing study effects and to lead to less biased results, in the case of dropouts, relative to models based on the randomized block/split-plot design approach (Lane 2008).

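### Adjustment for the pre-exposure score is left optional; it should be the primary analysis of the randomised exposure contrasts at T1

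*Protocol article*

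**What the plan says.** The Data analytic plan starts from a full factorial model: "The design of the study refers to a mixed four-way factorial ANOVA with exposure type" and group between subjects, with pre/post exposure and pre/post treatment within subjects. Two simplifications follow. One analyses the two sessions separately. The other is the adjusted analysis: "It can further be simplified to a two factorial model if, the pre-post-exposure difference is analyzed, using the pre values as a covariate". A methods reference is cited for it, but it is not made primary for any hypothesis.

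For the moderator hypothesis H-1.4 the plan is more definite: "the principle model contains the factors exposure and prepost-exposure plus the moderator of concern". There the pre-exposure score is a level of a factor, not a covariate.

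On estimation the plan says: "Note that we will use linear mixed models to analyze the data". It does not say whether the pre-exposure score is an outcome or a covariate in that model, or whether pre-exposure means are constrained equal across exposure arms.

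The Covariates section lists many adjustment variables, but not the outcome's own pre-exposure score. The Power analysis sizes H-1.1 and H-1.2 on effects that "correspond to the main effect experimental condition on pre-post exp.-differences".

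**The concern.** When pre and post scores are both free outcomes, the exposure effect is the exposure by pre/post interaction. With complete data this is the difference between arms in mean change. That estimate is valid under randomisation but is generally not the most precise one available. Conditioning on the pre-exposure score, or constraining its mean to be equal across arms, uses data already collected and removes variance that the change score keeps.

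Precision matters here. The Power analysis asks for 245 participants for H-1.2 and at least 309 for the physiological variables, against 250 planned. The adjusted and unadjusted analyses can also give different estimates in the same sample, and the Monitoring section exempts the cross-sectional data from its bar on preliminary analysis. The choice between them is best fixed before T1 results are seen.

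**Working it through.** **Inputs.** From the Power analysis: two-sided alpha .05, power .80, and f = .30, .16 and .18 with stated N of 90, 309 and 245. The last two f values are given there as upper bounds and are used here as point values. From Participants and Randomization: N = 250, groups of 100/50/50/50, 1:1 allocation. The pre-post correlation rho within group and arm is not in the article; it is assumed, over a range.

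**Step 1: reproduce the stated sample sizes.** Non-central F, 1 numerator df, noncentrality lambda = N·f².
- f = .30: 90 × .0900 = 8.10, power .804. The article says "the required sample size would be 90, (45 in each condition) to ensure a power > .80".
- f = .16: 309 × .0256 = 7.91, power .801.
- f = .18: 245 × .0324 = 7.94, power .801.

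The smallest N reaching .80 is 90, 309 and 245, exactly as stated.

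**Step 2: does a mixed model recover the precision by itself?** One simulated complete data set (N = 250, rho = .5):
- Mixed model, exposure by pre/post term: estimate 0.0054, SE 0.1253.
- Change-score regression: estimate 0.0054, SE 0.1253.
- Change regressed on exposure and pre-exposure score: SE 0.1068.

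It does not. The mixed model returns the change-score result unless the pre-exposure means are constrained.

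**Step 3: variance ratio.** With pre and post SDs s1 and s2:
- Change score: s1² + s2² − 2·rho·s1·s2.
- Adjusted: s2²(1 − rho²).
- Difference: (s1 − rho·s2)², which is never negative.

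With equal SDs the ratio is (1 − rho²) / [2(1 − rho)] = (1 + rho)/2, so the saving is (1 − rho)/2. In 4,000 simulated trials with the planned group sizes the ratio was 0.77 at rho = .5 (theory 0.75) and 0.89 at rho = .8 (theory 0.90).

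**Step 4: power at N = 250.** Eight cells, so 242 error df unadjusted and 241 adjusted. Unadjusted lambda is 250 × .0324 = 8.10 for f = .18 and 250 × .0256 = 6.40 for f = .16. Dividing by (1 + rho)/2 gives the adjusted lambda. This treats the pilot f as being on the unadjusted change scale.

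| Analysis | Saving | H-1.2, f = .18: power | N for .80 | Physiology H-1.1, f = .16: power | N for .80 |
|---|---|---|---|---|---|
| Change score | – | .81 | 245 | .71 | 309 |
| Adjusted, rho = .5 | 25% | .91 | 184 | .83 | 232 |
| Adjusted, rho = .8 | 10% | .85 | 220 | .76 | 278 |
| Adjusted, rho = .9 | 5% | .83 | 233 | .73 | 294 |

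For physiology, .80 is reached at N = 250 at rho = .6 (power .804) but not at .7 (.78).

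**Step 5: is the adjustment valid?** Participants in every group are randomised to exposure. At T1 the self-ratings and a baseline saliva sample are taken before the magazine is given (Experimental procedure). The T1 pre-exposure score therefore cannot be affected by exposure. Adjusting for it does not bias the exposure, exposure by group or exposure by moderator contrasts. At T2 this is not automatic: the T2 session (week 14) follows the T1 exposure and imagery induction (week 3), so its pre-exposure score is a post-randomisation measurement.

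**The case against.** The strongest reply is that the adjusted analysis is already in the plan, with a reference, and that choosing one primary model is a matter for a statistical analysis plan that is not shown. Part of this stands: if the sponsor uses the listed adjusted model, nothing is lost. But the article takes the pre/post factor model as its reference and gives it as the main model for H-1.4. Following that text yields the less precise estimate. The point is about the model the article names, not about missing detail.

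The second reply is that the size of the gain is unknown. This stands. Pre and post ratings use the same questionnaires in one session around a 10-minute exposure, so a correlation above .8 cannot be excluded, and the saving is then small. The Power analysis also does not say whether the pilot effect sizes came from a model that already adjusted for the pre-exposure score. If they did, the gain is already contained in f and the power increases above do not apply.

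Third, H-1.2 and H-1.3 predict effects at T1 that are weaker at T2. Separate adjusted analyses per session do not test that. This stands too, and a joint longitudinal model must be kept.

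Finally, the physiological measures, where the only stated shortfall lies, are secondary outcomes. That limits the stakes but not the argument.

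**Conclusion.** The point holds as a free gain in precision. For the T1 exposure contrasts, including exposure by group and exposure by moderator, adjusting for the pre-exposure score is unbiased and never less precise than the reference model, apart from about one degree of freedom. The saving is (1 − rho)/2: 25%, 10% or 5% at assumed correlations of .5, .8 or .9. The power figures rest further on equal pre and post SDs, on the pilot f being on the unadjusted change scale, and on f taken at its stated upper bound.

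A reader might infer more than the article supports:
- That the trial gives up a known share of variance. No correlation is given, and the loss arises only if the unadjusted model is used.
- That the sample sizes are wrong. They reproduce exactly and match a change-score analysis.
- That H-1.2 is short of participants. It needs 245 and 250 are planned; only the physiological outcomes have a stated gap, of 309 − 250 = 59. Adjustment closes that gap at rho = .5 but not at .8 or .9.
- That same-session adjustment is equally safe at T2. It is safe only if the T1 exposure has no carry-over.

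**What to change.** For the T1 exposure contrasts under H-1.1 to H-1.4, name one primary model: the post-exposure score (or the change) on exposure, group, exposure by group and the T1 pre-exposure score, with the moderator and its interaction with exposure for H-1.4. A mixed model with pre-exposure means constrained equal across exposure arms within group is equivalent.

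For T2 and for T1 versus T2, keep the joint longitudinal mixed model, with the T1 pre-exposure mean constrained or adjusted. Use the T2 same-session pre-exposure score only under a stated assumption of no carry-over from the T1 exposure.

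Report the unadjusted pre/post factor model as supportive. The cost is a few sentences in the analysis plan, ideally fixed before any T1 data are analysed. It needs no new data and no change to the planned sample size.

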Another factor probably influencing the susceptibility towards thin ideals promoted by mass media is the capacity to regulate emotions. The concept of emotion regulation (ER) encompasses strategies to regulate emotional experience and relies on the capability to correctly perceive, recognize, identify and express emotions (Thompson 1994; Gross 2007; Haynos & Fruzzetti 2011). A broad data base indicates that individuals who are not able to engage in effective management of emotional responses to everyday events experience longer and more severe periods of distress that may evolve into diagnosable depression or anxiety (Aldao et al. 2010). There is increasing data underlining the important role of ER in EDs (Tice et al. 2001; Guerrieri et al. 2008). Especially AN and to a somewhat lesser extent BN individuals seem to be affected by difficulties in identifying and labeling basic emotions (Harrison et al. 2010) compared to healthy controls. These problems are associated with more frequent use of maladaptive coping strategies (Harrison et al. 2010). According to the results of a current meta-analytic review (Haynos & Fruzzetti 2011) deficient ER correlates are found even after treatment of EDs and these deficiencies might be related to relapses. Nevertheless, it is an open question, whether these ER particularities are a correlate of acute ED episodes (the starving state) or whether they persist during remission (Oldershaw et al. 2012).

Figure 1 summarizes maintenance factors of disordered eating behavior according to Stice and colleagues (Stice et al. 2011) and highlights the moderators, which will be investigated in the current study. Other factors influencing the susceptibility towards the effects of media exposure will be considered as covariates (p. 16).

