## Methods/design

### Hypotheses

1.1 Exposure to *thin ideal* in contrast to *neutral* magazines causes an impairment of body image (FRS, VAS_B), affect (threeAS), eating behavior (VAS_E) and a physiological stress response (increase in mean salivary cortisol and alpha-amylase concentrations, HR and decrease in HRV).1.2 Exposure to *thin ideal* in contrast to *neutral* magazines is related to more pronounced negative body image (FRS, VAS_B), negative affect (threeAS), disordered eating behavior (VAS_E) and physiological stress response (increase in mean salivary cortisol and alpha-amylase concentrations, HR and decrease in HRV) in individuals with AN, BN, and the clinical control group (depression and SSD disorders) compared to the healthy control group, both at T1 and less at T2.1.3 Exposure to *thin ideal* in contrast to *neutral* magazines is related to more pronounced negative body image (FRS, visual VAS_B), negative affect (threeAS), disordered eating behavior (VAS_E) and physiological stress response (increase in mean salivary cortisol and alpha-amylase concentrations, HR and decrease in HRV) in individuals with AN and BN compared to the clinical control group, both at T1 and less at T2.1.4 The impact of thin ideal exposure on negative body image (FRS, VAS_B), negative affect (threeAS), disordered eating behavior (VAS_E) and physiological stress response (increase in mean salivary cortisol and alpha-amylase concentrations, HR and decrease in HRV) is moderated by cognitive style (TSFstate_B and/or TSFtrait_B) and ER capacity (see measures for detailed description). We expect stronger responses for participants with high TSF and low ER capacity.

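### The default H-1.4 model pools patients and healthy women without a group × exposure term, so it cannot separate moderation by ER or TSF from the diagnosis difference that H-1.2 predicts

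*Protocol article*

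**What the plan says.** The Data analytic plan describes the H-1.4 analysis in one sentence: "the principle model contains the factors exposure and prepost-exposure plus the moderator of concern, while the factor group can be added if required". It gives no criterion for when group is required and names no group × exposure term for this hypothesis.

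The hypothesis is worded for participants in general: "We expect stronger responses for participants with high TSF and low ER capacity". The Power analysis rests it on the whole sample: "With a sample of size of N = 250 also small to medium moderator effects (H-1.4) (Figure 1) could be detected". By the Participants section, that sample is 100 healthy women, 50 with AN, 50 with BN and 50 with mixed mental disorders.

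Three other statements bear on this model.

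- Power analysis, on response by group: "H-1.2 predicts that effects of the thin ideal induction are stronger for patients than for non-patients". The interaction is given as the "contrast: healthy vs. patients), which was small in the pilot study", with f below .18.
- Background, on ER by group: "BN individuals seem to be affected by difficulties in identifying and labeling basic emotions", with AN affected more strongly, both relative to healthy controls. The same section links poor emotion regulation to depression and anxiety.
- Covariates: severity measures may be adjusted for, depending on the hypothesis. Neither diagnostic group nor any covariate × exposure term is listed.

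**The concern.** An omitted group × exposure effect leaks into the exposure × moderator term when two things hold: the response to exposure differs by group, and the moderator differs by group. The protocol predicts the first in H-1.2 and reports the second for ER. The default H-1.4 model leaves out the term that would separate the two.

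The moderators are described as a main focus of the study, and the Discussion draws intervention proposals from them (training in ER, restructuring of distorted beliefs). A positive H-1.4 result from the pooled model could mean that ER or TSF shapes the response. It could equally mean that patients respond more and also score worse on ER. The second reading gives no separate support for those proposals. Because the condition for adding group is open, the choice could also be made after both results are seen.

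**Working it through.** **1. The plan's own figures.** The Power analysis works by "assuming two-sided tests with Alpha = .05 and Beta = 0.2 (Power = 0.8" and concludes for H-1.2: "Thus the total sample size should be at least 245". For a 1-df F test with noncentrality N × f², f = .18 at N = 245 gives power .801, and 244 gives just under .80. The other two figures also reproduce (f = .30: 90; f = .16: 309). No stated number is wrong; the point is the choice of model.

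**2. Inputs.** From the protocol: 100 healthy women and 150 patients (patient share p = .6), 1:1 allocation, two-sided alpha .05, and group × exposure f up to .18. Assumed, because the protocol gives no size: a patient-minus-healthy gap d on the moderator of 0, 0.5, 1.0 or 1.5 within-group SD, scored so that higher is worse. The outcome is the pre-post exposure change with residual SD 1, so exposure × moderator on the change stands for exposure × prepost-exposure × moderator. The moderator has no effect inside any group.

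**3. Spurious coefficient.** The group × exposure difference is δ = f / √(p(1−p) × 0.25) = .18 / √(.24 × .25) = .735. If all patients are shifted, the pooled coefficient per SD of moderator is

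δ × .24d / √(1 + .24d²).

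At d = 0.5, 1.0 and 1.5 this is .086, .158 and .213. Its standard error is about 1 / √(250 × .25) = .126, so the expected z is about 0.68, 1.25 and 1.69. The chance of exceeding 1.96 in absolute value is then about 10%, 24% and 39%. Simulation gives slightly less, because the omitted interaction also adds residual variance.

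If only the 100 AN and BN patients are shifted, while all patients respond more, .24d in the numerator becomes (.4 − .6 × .4)d = .16d. The coefficients are then .057, .106 and .142.

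**4. Simulated rejection rates for a null within-group moderator** (5,000 to 10,000 trials per setting for the first, third and fourth rows; ranges show the spread between runs)

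| Setting | d = 0 | 0.5 | 1.0 | 1.5 |
|---|---|---|---|---|
| No group, f = .18, all patients shifted | 5% | 9–10% | 22–23% | 37–38% |
| No group, f = .18, AN and BN only shifted | 5% | 7–8% | 13% | 19–20% |
| No group, f = .10, all patients shifted | 5% | 7% | 10–11% | 15–16% |
| Group main effect only, f = .18, all patients shifted | 5% | 10% | 23% | 37–38% |
| Group and group × exposure, f = .18 | 5% | 5% | 5% | 5% |

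The main-effect row shows that what matters is the interaction with exposure, not group as such. The same logic applies to severity covariates entered as main effects.

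**5. What adjustment costs.** The share of moderator variance lying between groups is .24d² / (1 + .24d²): 5.7%, 19.4% and 35.1% at d = 0.5, 1.0 and 1.5. A moderator effect with 80% power in the pooled model has expected z of about 2.80. Adjustment multiplies this by √(1 − share), giving 2.72, 2.51 and 2.26, and power of about 78%, 71% and 62%.

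**The case against.** **The estimand.** H-1.4 is not restricted to variation inside groups, and the study aims include explaining differential susceptibility. If ER or TSF is the reason patients respond more, conditioning on group × exposure removes part of the hypothesised effect. This stands. It is why the pooled model should be kept and why its rejections cannot simply be called false. It does not rescue the pooled model as the only test, because that model cannot tell the two explanations apart.

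**The text permits group.** In a factorial model, adding a factor would normally bring its interactions, and a fuller plan may say when. This stands in part: omission is the default, not a certainty. The default is nevertheless written down, it has no criterion, and the term that matters is not named.

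**The size.** A reader might infer that H-1.4 will be wrongly confirmed in a third to a half of trials. The documents do not support that. The pilot f is an upper bound, no moderator gap is stated, and shifting only the eating-disorder groups roughly halves the larger rates (a larger response in those groups, as H-1.3 predicts, would raise them again).

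**The moderators.** A reader might also infer that ER deficits are confined to eating disorders and that TSF is known to differ by group. The Background links poor ER to depression and anxiety as well, and says TSF can be induced in both patients and controls without comparing their levels. TSFstate_B and the heart-rate part of the ER index are measured during the experiment, and the simulated baseline moderator does not represent them.

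**Conclusion.** The concern holds as a matter of model specification and should be fixed, though it does not undermine the trial. The default H-1.4 test does not isolate moderation by ER or TSF from the diagnosis difference. The direction follows from the protocol's own statements for ER; for TSF it is plausible but undocumented.

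The size rests on assumptions. With no moderation inside any group, rejection rises from 5% to somewhere between about 7% and 38% across gaps of 0.5 to 1.5 SD, depending on f and on which patients differ. There is no excess if the groups do not differ on the moderator. The documents do not support the stronger conclusion that a positive pooled result would be false: it may partly reflect a real effect that runs through diagnosis.

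**What to change.** In the Data analytic plan, replace the clause that makes group optional for H-1.4 with a rule of three parts:

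1. H-1.4 is always also tested with the four-level group factor and group × exposure (× prepost-exposure) in the model.
2. The pooled and group-adjusted moderator estimates are reported side by side.
3. Moderation independent of diagnosis is claimed only from the group-adjusted model.

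Centring the moderator within group is not needed, because the tested coefficient is the same once group and group × exposure are included.

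In the Power analysis, qualify the H-1.4 remark. It describes the pooled model; an effect with 80% power there has about 78%, 71% or 62% power after adjustment at gaps of 0.5, 1.0 or 1.5 SD.

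The edit is a few sentences and changes neither recruitment nor data collection. The real cost is that loss of power, plus a few degrees of freedom.
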